## Discussion

This article presents a detailed description of a cluster RCT with the aim to investigate the effects of a patient-centred internet programme supporting self-titration of insulin therapy in type 2 diabetes patients compared with standard-of-care physician-driven insulin titration. This will provide researchers and health care providers the opportunity to critically review the methodological quality, the background theory and the practical issues of the RCT [50]. The key element of this trial is that this web-based self-management intervention in the treatment of T2DM patients is designed to enhance patient empowerment, what could result in adequate self-management behaviours (including insulin dose adjustments) that in turn will help to improve and sustain glycaemic control.

Besides the focus on increasing patient empowerment, a strength is the construction of the intervention guided by the self-regulation theory of Leventhal. The use of a theory in general is important for several reasons. A theory helps to design the intervention, it provides a good base for the evaluation of the intervention ('how does it work (or not)?') and it will enable other researchers to refine the theory or intervention [51,52]. In designing the internet programme of our study we have used an important aspect of the self-regulation theory: providing feedback [32]. This will promote effective self-evaluation of health and self-care behaviours and adjustment of cognitive representations and beliefs and subsequent glycaemic control. We will evaluate our theoretical background by investigating if the intervention has increased self-efficacy and changed illness perceptions. Another strength is the use of internet technology. A large part of the population in the Netherlands (86% of all households in 2008) has access to the internet [53]. Internet can meet different needs of patients, like the need of adequate information and continue, access to care [54]. E-health applications are upcoming and the Dutch Patient Consumer Federation (NPCF) has published a vision document, stimulating e-health developments [54].

The intervention will be provided to patients from two different regions in the Netherlands: Amsterdam (an urban region) and Twente (a rural area), which should add to external validity, i.e. generalisability. If our intervention proves to be more effective than care as usual, the internet programme could be widely implemented in general practices in the Netherlands.

There are also some limitations in the study design. We will compare the intervention with usual care. In the Netherlands, most general practitioners or their practice nurses take care of insulin titration, but there is no strict insulin regimen. That means that usual care is not the same in each practice. However, in the sample size calculation we accounted for this by multiplying with an intercorrelation coefficient, providing sufficient power to prevent this bias. Another limitation is the use of different co-medication next to insulin. Except for thiazidediones, metformin and SU-derivates can be continued. That means that there can be some additional effect of oral hypoglycaemic agents on HbA1c. Because we aim at a close approach to the real life situation, the individual GP is free to decide about continuing or stopping the oral medication. Furthermore, the addition of short-acting insulin analogues or even switching to another insulin could be needed in individual patients. At that point the internet programme can not be used for insulin dose advices in the intervention group. All co-medication will be recorded and in analyses used as possible confounder or effect modifier.

The self-titration of insulin and computer-based adjustment of insulin dose has been investigated before. However, the proposed trial is to our knowledge, the first to assess the effects of a web-based guided insulin self-titration intervention in previous insulin-naive T2DM patients. It can make a considerable contribution to the evidence of the importance of the patient empowerment approach in improving diabetes care, making use of modern technology.

The trial has started in January 2009 and the first results will be available in 2011.

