The process of using the online-diary will continue until the patient has reached a normal FBG (FBG between 4.0 and 7.0 mmol/L). At that point he/she is advised to make a 5-point day-curve. Dependent on the value of one of the measured glucose values, the internet programme will automatically respond with a feedback question or will give advice to repeat the day-curve after 2 days. When a stable insulin dose is reached (all measurements are within the range of 4.0 – 9.0 mmol/L), it is advised to measure FBG once a week. When repeated day-curves (4 day-curves in approximately one week) are not within normal range, it is advised to contact the GP or practice nurse. Protocols for how to act in different situations will be provided to the GP's. If another or additional (short-acting) insulin is started, patients will not be able to use the internet programme any longer. This is also the case if the insulin dose exceeds 80 IE. If the GP or practice nurse needs extra advice, a diabetes nurse from the Diabetes Research Center can be contacted.

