### Outcome assessment

Outcome measurements are assessed by means of self-administered web-based questionnaires (accessible with a log-in name and password provided by email for both the intervention and the control group) and physical examination at the general practices. If questionnaires are not completed within one week an email-reminder will be sent to the participants. In case of no response, a phone call to their general practice will be made by the investigator. Physical and clinical data will be obtained from the usual 3-monthly check-ups for diabetes patients in their own practice. The practice nurse or GP will record patients' diabetes duration, co-morbidity, pre-existing diabetes complications, and medication at baseline.

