#### Other data collection

• *Patient characteristics, internet use (assessed on baseline):* demographic variables (age, gender, marital status, nationality, socio-economic state); experience in use of the internet; smoking (cigarettes/day) and alcohol (glasses/day) use.

• *Medication, diabetes care use:* Total required insulin dose (every 3 months this will be self-reported in the web-based questionnaire); Time delay to reach stable insulin dose (i.e. HbA1c < 7.0%); (Oral) medication changes (data obtained from pharmacy and GP); Frequency of contacts with health care providers (every 3 months this will be self-reported in the web-based questionnaire).

• *Physical and clinical measurements (assessed on the usual diabetes check-ups in the general practices every 3 months):* Weight; Length; Blood pressure; FPG; Lipid spectrum: triglycerides, total cholesterol, and HDL- and LDL-cholesterol (assessed at baseline and after 12 months).

• *Depression (assessed on baseline, 3 and 12 months):* The Patient Health Questionnaire is used to assess the general health of the patient. This brief PHQ (PHQ-9) consists of 9 items, measured on a four-point scale, in order to assess depressive disorders during the last two weeks [47]. This will be assessed because of the possible confounding effect depression has on self-performing activities.

• *Insulin Perceptions (assessed on baseline, 6 and 12 months):* Negative perceptions in insulin naive and insulin-treated patients regarding insulin treatment and changes therein are assessed with the Insulin Initiation Perception Scale (IIPS), a short version of the Insulin Treatment Appraisal Scale (ITAS) [48].

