### Analysis

Descriptive statistics (means ± SD or median and inter quartile range as appropriate) will be used to describe the study sample with regard to demographics and baseline (clinical) characteristics. On the basis of an intention-to-treat analysis, differences in changes between the intervention group and control group are calculated with 95% confidence intervals at 3, 6 and 12 months for both primary and secondary outcomes.

Using *t*-tests and multiple linear regression – duly adapted for the multilevel structure of the data – we will compare changes in HbA1c, number of hypoglyceamias, quality of life, treatment satisfaction, illness and insulin perceptions and confidence in diabetes self-care scores at different time intervals between the groups, with adjustment for important prognostic factors like age, diabetes duration, medication and level of education where appropriate. Separate analyses of possible effect modifiers (i.e. age, depression, previous internet use) will be performed in order to gain a better understanding as to who benefits most from the intervention.

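### Co-medication is a possible confounder or effect modifier with no limit to baseline, so an HbA1c estimate adjusted for it may depart from the intention-to-treat effect

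*Protocol article*

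**What the plan says.** The Discussion names varying co-medication as a limitation. It says that "the individual GP is free to decide about continuing or stopping the oral medication" and that "the addition of short-acting insulin analogues or even switching to another insulin could be needed in individual patients". It then gives the analytic response: "All co-medication will be recorded and in analyses used as possible confounder or effect modifier".

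The Analysis section promises intention-to-treat differences in change with 95% confidence intervals. It names t-tests and multilevel-adapted regression, "with adjustment for important prognostic factors like age, diabetes duration, medication and level of education where appropriate". Its effect modifiers are age, depression and earlier internet use; co-medication is not among them.

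Two sets of medication data are collected. Outcome assessment has the practice record "pre-existing diabetes complications, and medication at baseline". Other data collection adds changes in medication during follow-up, taken from pharmacy and GP.

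**The concern.** A confounder of a randomised comparison has to be in place before allocation. Practices are randomised first and their patients follow the practice's arm (Study procedure), and GPs and practice nurses know the arm (Blinding). Stopping an oral agent, adding insulin or switching insulin during the trial therefore comes after allocation and may respond to it. Such a variable can lie on the path from programme to HbA1c. If unmeasured prognosis also drives it, adjustment can create an association between arm and prognosis that randomisation had removed.

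The protocol itself ties one of these changes to the intervention: "If another or additional (short-acting) insulin is started, patients will not be able to use the internet programme any longer". Adjusting for added or switched insulin, or splitting patients by it, partly conditions on having left the programme. That moves towards an as-treated comparison in a trial that promises intention to treat. Effect modification by a variable set after allocation is likewise not protected by randomisation.

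**Working it through.** **1. Is the adjustment limited to baseline?** The Discussion says all co-medication, and the sentences just before it describe decisions during the trial. The Analysis section gives medication no date. Baseline medication is recorded separately, but neither section restricts adjustment to it. The two sections also differ on whether co-medication is an effect modifier.

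**2. Could changes depend on arm?** In the intervention group, repeated out-of-range day-curves lead to advice to contact the practice. In the control group, titration and contacts vary by practice. The routes to a medication change differ, so dependence on arm is possible. The documents do not show that it will occur.

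**3. Size when nothing unmeasured drives both change and HbA1c.** The documents give no change rates or effects, so every value in steps 3 and 4 is assumed. Let D be the programme effect at fixed co-medication, g the effect of a medication change on HbA1c, and p1 and p0 the proportions changed in intervention and control. Then

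- intention-to-treat effect = D + (p1 − p0)·g
- adjusted linear coefficient = D
- adjusted minus intention-to-treat = −(p1 − p0)·g

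With D = −0.50 and g = −0.5:

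- p0 = 0.30, p1 = 0.10: (−0.20)(−0.5) = +0.10. The intention-to-treat effect is −0.40 and the adjusted one −0.50, an overstatement of 0.10 (0.10/0.40 = 25%).
- p0 = 0.10, p1 = 0.25: (0.15)(−0.5) = −0.075. The intention-to-treat effect is −0.575 and the adjusted one −0.50, an understatement of 0.075.
- p1 = p0: no difference.

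**4. Size when unmeasured prognosis U may drive both.** Large-sample simulation, 1,000,000 patients per case, without clustering because the question is bias and not precision. Log-odds of a change = −1 + a·arm + b·U. HbA1c change = −0.50·arm + g·change + 0.6·U + noise with SD 1. The outcome SD is about 1.2. U is inactive on medication at b = 0 and active at b = 0.7.

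| a | b | g | Rate control / intervention | Unadjusted (ITT) | Adjusted | Gap |
|---|---|---|---|---|---|---|
| 0 | 0 | −0.6 | 0.269 / 0.268 | −0.502 | −0.502 | 0 |
| 0 | 0.7 | −0.6 | 0.289 / 0.289 | −0.499 | −0.499 | 0 |
| −1 | 0 | −0.6 | 0.270 / 0.119 | −0.412 | −0.503 | −0.091 |
| 1 | 0 | −0.6 | 0.270 / 0.500 | −0.637 | −0.499 | +0.138 |
| −1 | 0.7 | −0.3 | 0.288 / 0.138 | −0.455 | −0.442 | +0.013 |
| −1 | 0.7 | −0.6 | 0.288 / 0.137 | −0.410 | −0.443 | −0.033 |
| 1 | 0.7 | −0.3 | 0.289 / 0.502 | −0.563 | −0.581 | −0.018 |
| 1 | 0.7 | −0.6 | 0.288 / 0.499 | −0.626 | −0.580 | +0.046 |

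A negative gap means that adjustment overstates the benefit. Where U is active and the rates differ, the adjusted value equals neither the intention-to-treat effect nor the direct effect of −0.50. The sign changes with g at almost the same rates. In these cases the two errors partly cancel, so the gaps are smaller than without U.

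**5. Sample size.** The plan's figure reproduces. 2·(1.2·(1.960 + 0.842)/0.5)² = 90.4 per group (stated 90). The design effect is 1 + 3·0.05 = 1.15. 90·1.15/4 = 25.9, so 26 practices per group. 2·26/0.85 = 61.2, so 62 practices and 62·4 = 248 patients. Limiting covariates to baseline changes none of this.

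**The case against.** The Discussion says *possible*, and the Analysis section adjusts only where appropriate. Intention-to-treat differences and t-tests are planned as well. A reader might infer that the primary HbA1c estimate will be biased, but the documents do not support that. They do not say that medication changed in follow-up enters the primary model, and an unadjusted estimate remains available. Only an adjusted or effect-modifier analysis is exposed.

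The Analysis section can fairly be read as meaning baseline, since medication stands there beside age, diabetes duration and education. The Discussion opens the topic as drugs taken next to insulin, so it is unclear whether added or switched insulin counts as co-medication. Practices are randomised before patients are invited, so oral treatment at entry could differ between arms, and adjusting for that is defensible. All of this stands. It narrows the point to medication after allocation, which the word *all* takes in and which nothing in the article excludes.

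Covariate detail is often left to an analysis plan. Here, however, the article positively states a use of all co-medication, and its Setting section presents it as the final protocol.

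A reader might extend the point to depression, because the article says of the PHQ-9: "This will be assessed because of the possible confounding effect depression has on self-performing activities". That does not follow. The sentence explains why depression is measured. The Analysis section names depression only as a modifier, to learn who benefits most, and nothing says that follow-up scores enter the HbA1c model.

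**Conclusion.** The point holds for adjusted and effect-modifier analyses of HbA1c. As written, the plan lets medication changed after allocation enter them, and such an estimate may not be the intention-to-treat effect it would be taken for. The direction cannot be predicted and the size cannot be derived from the documents. Under the assumed values the gap runs from zero to about 0.14 HbA1c percentage points, a little over a quarter of the 0.5 target (0.138/0.5 = 0.28). It is zero if changes are unrelated to arm and prognosis selects patients for a change in the same way in both arms. The choice of adjustment should not stay open until the data are seen.

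**What to change.** State in both the Analysis section and the Discussion that only medication recorded at baseline may enter the HbA1c models as covariate or effect modifier. Report follow-up changes in oral agents, added or switched insulin, and insulin dose by arm, either descriptively or in an analysis labelled as mediation or sensitivity. Align the two sections on whether baseline co-medication is an effect modifier.

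The cost is wording only. Baseline medication and follow-up changes are already collected, the sample size stays at 248, and no clinical rule changes.

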## Abbreviations

T2DM: type 2 diabetes mellitus; HbA1c: glycated haemoglobin; GP: general practitioner; ADA: American Diabetes Association; IBCT: interactive behaviour change technology; EASD: European Association for the Study of Diabetes; FPG: fasting plasma glucose.
